## Abstract

**Background:**

Portopulmonary hypertension (PoPH) is a subtype of the pulmonary arterial hypertension (PAH) associated with portal hypertension. There is a dissociation between the proportion of PoPH in PAH and that of PoPH in patients with liver cirrhosis, suggesting PoPH underdiagnosis and an incomplete understanding of this entity in the clinical setting. Specifically, real-world data in Japan is largely unknown as compared with in Europe and the United States. The present study aims to elucidate the prevalence and etiology of PoPH in Japanese patients with chronic liver disease.

**Methods and design:**

In this prospective, single-center, observational investigation of PoPH patients with chronic liver disease, a targeted 2,500 Japanese adult patients regularly visiting Shinshu University Hospital in Matsumoto, Japan, for chronic liver disease will complete a standardized questionnaire on the presence of PoPH symptoms. If the respondent has signs of possible PoPH, ultrasound echocardiography (UCG) will be performed as a primary screening. In the case that UCG findings indicate pulmonary hypertension, the patient will be referred to a cardiologist for further evaluation, whereby a definitive diagnosis PoPH can be made. PoPH prevalence and etiology will be investigated at the time of diagnosis. Afterwards, patients with PoPH will be followed for five years for determination of survival rate.

**Discussion:**

This study will reveal the prevalence, etiology, and 5-year survival rate of PoPH in Japanese patients with chronic liver disease.

**Trial registration:**

This study is being performed at Shinshu University following registration as UMIN 000042287 on October 29, 2020.

## Introduction

Portopulmonary hypertension (PoPH) is defined as pulmonary arterial hypertension (PAH) complicated with portal hypertension most often due to chronic liver disease [1, 2]. PoPH occurs in 5–15% of patients with PAH [3, 4] and is reportedly found in 2–6% of portal hypertension cases and 1–2% of cases of liver cirrhosis [3, 5]. The real-world data on PoPH in Japan are largely unknown as compared with in Europe and the United States [3, 4]. Atsukawa et al. earlier retrospectively analyzed 186 patients who simultaneously received hepatic vein and pulmonary artery catheterization to investigate the prevalence of PoPH and identified two patients (1%) with PoPH. However, the exact prevalence of PoPH remains unclear in Japanese patients with chronic liver disease, with the low prevalence of PoPH suggesting underestimation and an incomplete clinical picture of PoPH in Japan.

The pathogenesis of PoPH is uncertain. In addition to genetic predisposition [6], thromboembolism in the portal venous system [7], inflammation [8], hyperdynamic pulmonary circulation [9], and imbalance of vasoconstrictive and vasodilatory mediators due to a reduction in affected liver metabolism [10] have been associated with PoPH development. Indeed, higher rates of PoPH were reported in patients with end-stage liver disease undergoing liver transplantation, although the prevalence of PoPH was not influenced by liver disease severity [4, 10]. No gender differences have been detected in PoPH prevalence [11], although female patients with autoimmune hepatitis (AIH) may have a higher risk of PoPH development [12]. Accumulating evidence suggests that the existence of chronic liver disease, including AIH, hepatitis C virus (HCV) infection, and alcoholic liver disease (ALD), are linked to PoPH onset [11]. However, it is unknown which chronic liver diseases are prominently involved in PoPH development in Japanese patients.

The clinical manifestations of PoPH are identical to those of PAH, i.e., dyspnea on exertion, atypical chest pain, elevated jugular venous pressure, leg edema, and others [1, 13], all of which are considered non-specific symptoms of PoPH. Therefore, the threshold for suspecting PoPH should be low since patients with chronic liver disease often exhibit dyspnea for a variety of reasons; a precise but simple medical history interview is needed for selecting candidate patients for ultrasonic echocardiography (UCG) and further examination. Moreover, as complicating PoPH in patients with chronic liver disease is a poor prognostic factor despite targeted therapy intervention [11], early detection and intervention is needed to improve prognosis in Japanese patients with PoPH.

The present study aims to address the following clinical research questions in Japanese patients with chronic liver disease:

Observational study 1: What is the prevalence of PoPH in Japanese patients with chronic liver disease?Observational study 2: What are the etiology of liver disease and clinical pathophysiology of PoPH?Observational study 3: What is the 5-year survival rate of PoPH, and which factors influence overall survival?

## Materials and methods

This is an ongoing, prospective, single-center, observational study that will run from October 1, 2020 to October 30, 2027. The study flowchart is presented in Fig 1. This study was reviewed and approved by the Institutional Review Board of Shinshu University School of Medicine (approval number: 4891) on September 29th, 2020. Written informed consent will be obtained from all subjects. The study is being conducted according to the principals of the Declaration of Helsinki.

**Fig 1 pone.0249435.g001:**
[figure not shown]
The study flowchart. Abbreviations: PH, pulmonary hypertension; PoPH, portopulmonary hypertension.

### Target population

We are targeting a total of 2,500 adult patients who regularly visit Shinshu University Hospital in Matsumoto, Japan, for chronic liver disease observation or treatment.

#### Inclusion criteria

Patients in the analysis must meet all three inclusion criteria, as follows: 1) over 20 years of age, 2) having chronic liver disease, and 3) having symptoms suggestive of PoPH, as summarized in Table 1.

**Table 1 pone.0249435.t001:** Inclusion and exclusion criteria.

Inclusion criteria
Patients must meet all of the following items:
1. Age >20 years
2. Having chronic liver disease
3. Having any symptom indicating portopulmonary hypertension
Exclusion criteria
Patients with any of the following items are excluded:
1. Having history of chronic heart failure
2. Having history of pulmonary arterial hypertension from any other cause.
3. Unable to be followed at our hospital

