### Trial design and follow-up

Participant registration for the study will run from October 1, 2020 to October 30, 2022. All participants will answer the written questionnaire described in Table 2 in the outpatient clinic of Shinshu University Hospital. If at least one question is positive, informed consent will be obtained from the individual for enrollment in the study. Then, the participant will undergo ultrasound echocardiography (UCG) as a first-line screening. If the participant exhibits UCG-positive findings indicating a high probability of PoPH as shown in Tables 3 and 4, the patient will be referred to a cardiologist in the Department of Cardiology for further evaluation, whereby a definitive diagnosis will be made by right heart catherization findings as shown in Table 5. The frequency of PoPH patients will be analyzed (Observational study 1) along with the etiology of PoPH in chronic liver disease (Observational study 2).

**Table 2 pone.0249435.t002:** Standardized questionnaire on symptoms suggesting portopulmonary hypertension (translated from Japanese; respondents indicate “yes” or “no”).

1) Do you feel you cannot work comparably to other people of the same age and gender?
2) Do you feel you cannot move as fast as other people do?
3) Do you feel you cannot move at the same pace as others?
4) Do you need rest when climbing stairs or carrying heavy loads?
5) Do you ever experience shortness of breath?
6) Do you ever experience faintness?
7) Do you ever experience tiredness and/or persistent malaise?
8) Do you ever experience dizziness and/or vertigo?
9) Do you ever experience facial edema and/or pretibial edema?

**Table 3 pone.0249435.t003:** Echocardiographic probability of PAH in patients having symptoms indicative of PAH [21].

Peak tricuspid regurgitation velocity (m/s)	Presence of other echo PH signs	Echocardiographic probability of PAH
≤2.8	No	Low
≤2.8	Yes	Intermediate
2.9–3.4	No	
2.9–3.4	Yes	High
>3.4	Not required	

Abbreviations: PAH, pulmonary artery hypertension; PH, pulmonary hypertension.

**Table 4 pone.0249435.t004:** Echocardiographic signs suggesting PAH used to assess the probability of PAH in addition to tricuspid regurgitation velocity measurement in Table 3 [21].

A: Ventricles	B: Pulmonary artery	C: Inferior vena cava and right atrium

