#### Endpoints

The primary endpoint in this study is the prevalence of PoPH in Japanese patients with chronic liver disease and its etiology (Observational study 1 and study 2). The secondary endpoint is the overall 5-year survival rate (Observational study 3).

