#### Statistical analysis

The prevalence of PoPH will be examined at the time of PoPH diagnosis. The clinical pathophysiology of PoPH will be evaluated by multivariate analysis using the following factors: etiology of liver disease, age, sex, height, weight, diagnosis, medication history, smoking history, drinking history, NYHA classification, 6-minute walking distance, laboratory tests, FibroScan^®^ results, the presence of cancer, right heart catheter findings (mean pulmonary artery pressure, right atrial pressure, pulmonary artery wedge pressure, and cardiac index), and echocardiographic findings. The changes in clinical symptoms, UCG findings, and hepatic function will be also be examined before and after treatment. Continuous variables will be statistically evaluated by means of the Mann–Whitney U test, while categorical variables will be analyzed using the chi-square test.

Overall survival rate will be examined using the Kaplan–Meier method. Independent factors influencing overall survival will be assessed by Cox regression analysis with stepwise methods.

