## Discussion

This prospective observational study aims to clarify the clinical characteristics of PoPH in the Japanese population. Both cirrhosis and non-cirrhosis stage patients may become complicated with PoPH. Although the frequency of PoPH in patients with cirrhosis has been described, PoPH prevalence in chronic liver disease remains unknown. Unlike in cohorts from Western countries, where the proportion of ALD is high [24], viral hepatitis-related chronic liver disease is more prevalent in Japan. In the few studies on PoPH in Asia and Japan investigating disease prevalence and incidence, AIH and PBC were found to be more likely complicated with PoPH [5]. However, due to the small number of cases included in those investigations, the clinical picture of PoPH is uncertain. The present study will seek to answer these important questions.

A retrospective study from the United States showed that patients untreated for PoPH had a poor 5-year survival rate of 14%, which was associated with the delayed diagnosis of PoPH [25]. One reason could be that up to 60% of patients with PoPH were asymptomatic [1]. PoPH cases are contraindicated for liver transplantation due to high operative mortality and poor prognosis. Early intervention for PoPH is therefore essential to overcome this issue and improve prognosis. An established standardized questionnaire may be helpful in PoPH screening as a first diagnostic step.

During the past two months, this study’s questionnaire has been administered to 300 patients with chronic liver disease meeting the inclusion criteria. Interestingly, 153 patients (51.0%) described symptoms suggestive of PoPH. Among them, 36 patients providing informed consent underwent further UCG analysis. Two cases were found to have PAH, while one case was diagnosed as having PoPH. As previously reported, the prevalence of PoPH is expected to be very low. By recruiting a sufficient number of patients, however, we aim to determine the actual status of PoPH in Japan.

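### The stated analysis set (symptomatic patients who consent) does not match the primary endpoint of PoPH prevalence in all patients with chronic liver disease, and the direction of the resulting bias is not identified

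*Protocol article*

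**What the plan says.** All references are to the protocol article.

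- **Who is analysed.** Inclusion criteria: "Patients in the analysis must meet all three inclusion criteria". The third, repeated in Table 1, is "Having any symptom indicating portopulmonary hypertension".
- **Who is enrolled.** Trial design and follow-up: "If at least one question is positive, informed consent will be obtained from the individual for enrollment in the study". UCG comes after that, and right heart catheterization only after a positive UCG.
- **What is claimed.** Endpoints: "The primary endpoint in this study is the prevalence of PoPH in Japanese patients with chronic liver disease and its etiology". The first research question in the Introduction and the Conclusions make the same claim. None restricts it to patients with symptoms.
- **How prevalence is computed.** Statistical analysis gives only timing: "The prevalence of PoPH will be examined at the time of PoPH diagnosis". Trial design and follow-up says that a frequency will be analysed. Neither names a denominator.
- **What the 2,500 are.** In the Abstract they are the patients who attend the hospital "for chronic liver disease will complete a standardized questionnaire on the presence of PoPH symptoms", that is, everyone screened. Target population likewise sets no symptom requirement. Sample size estimation arrives at 2,500 recruited cases after mentioning the symptomatic half and 20% refusal.
- **Early experience.** The Discussion says that the "questionnaire has been administered to 300 patients with chronic liver disease meeting the inclusion criteria", then reports that 153 of the 300 had symptoms, 36 consented and had UCG, and one had PoPH.

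**The concern.** Read literally, the analysis divides PoPH cases by symptomatic patients who consented. That is a prevalence among symptomatic consenters, which is a different quantity from the endpoint. The article also moves between populations. It describes 300 respondents as meeting the inclusion criteria when 300 - 153 = 147 of them reported no symptom and so fail the third criterion.

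This is the primary endpoint, and the article's case that PoPH is underestimated in Japan rests on comparing prevalence figures. The Introduction cites 1–2% in cirrhosis, a range only 2-fold wide. A free choice among denominators that differ by more than this could decide how the result is read.

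The obvious alternative, cases over all respondents, does not settle the matter. It counts symptomatic patients who never had UCG as free of disease.

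**Working it through.** **Inputs.** Sample size estimation: about half symptomatic, 20% decline consent. Discussion: 300 respondents, 153 symptomatic, 36 with consent and UCG, 1 PoPH case; up to 60% of PoPH patients asymptomatic in a cited source. The article's symptomatic fraction reproduces: 153/300 = 51.0%.

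**1. Candidate denominators, pilot counts (exact Clopper–Pearson 95% CI)**

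| Denominator | Estimate | 95% CI |
|---|---|---|
| 36 symptomatic, consented, UCG done | 1/36 = 2.78% | 0.07–14.5% |
| 153 symptomatic | 1/153 = 0.65% | 0.02–3.59% |
| 300 respondents | 1/300 = 0.33% | 0.01–1.84% |

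The spread is 300/36 = 8.33, made up of 300/153 = 1.96 for the symptom restriction and 153/36 = 4.25 for incomplete uptake (36/153 = 23.5%).

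**2. The same spread at the planned rates.** 1/(0.5 × 0.8) = 2.5, made up of 1/0.5 = 2.0 for symptoms and 1/0.8 = 1.25 for refusal.

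**3. A two-stage estimate.** Suppose that those who had UCG represent all questionnaire-positive patients, and that no questionnaire-negative patient has PoPH. Then

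P(positive) × P(PoPH | positive, UCG done) = 0.51 × 1/36 = 1.42%.

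Against this, the literal analysis set is 2.78/1.42 = 1.96 times too high, and cases over all respondents is 1.42/0.333 = 4.25 times too low.

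**4. Relaxing the zero in questionnaire-negatives.** Let *a* be the share of PoPH cases that are asymptomatic, taken here as questionnaire-negative. Prevalence in chronic liver disease is then 1.42%/(1 - *a*), and the ratio of the literal figure to it is (1 - *a*)/0.51.

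| *a* | Prevalence | Literal figure (2.78%) relative to it |
|---|---|---|
| 0 | 1.42% | 1.96 (too high) |
| 0.49 | 2.78% | 1.00 |
| 0.60 | 3.54% | 0.78 (too low) |

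The sign changes at *a* = 1 - 0.51 = 0.49, which lies inside the range that the article itself cites.

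**5. The two meanings of 2,500.** If they are respondents, the analysis set is about 2,500 × 0.5 × 0.8 = 1,000. If they are symptomatic consenters, 2,500/0.4 = 6,250 patients must be screened, against 4,800 + 300 = 5,100 attending in a year. The two readings are different studies.

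All pilot percentages rest on one case. They illustrate the ratios and are not evidence about the true prevalence.

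**The case against.** The strongest reply is that the article never writes down a denominator. The Abstract and Target population treat all attending patients as the study population, the Discussion counts all 300 respondents, the flowchart is not shown, and a full protocol or analysis plan may name the denominator. This stands in part: it cannot be said that the investigators have settled on the wrong denominator. It does not remove the point, because the article is not silent on who is analysed. It states a rule that excludes patients without symptoms, and that rule conflicts with the endpoint and with those other sections.

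A reader might infer an 8-fold error. The documents do not support that. The 8.3 compares two candidates that are both biased (in opposite directions if questionnaire-negatives have no PoPH), and more than half of it on the ratio scale comes from uptake in the first two months of an ongoing study. The article does not say whether UCG was still pending for others. At the planned rates the spread is 2.5.

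A reader might also infer that the literal analysis overstates prevalence. That holds only if few PoPH cases are questionnaire-negative. With the article's upper figure of 60% asymptomatic, it understates.

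The same argument limits the remedy: a two-stage estimate sets PoPH to zero in questionnaire-negatives, so at 60% asymptomatic it is 1/(1 - 0.6) = 2.5 times too low. It has to be labelled and bounded accordingly. Elaborate weighting for UCG uptake would also be fragile with very few cases.

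Finally, counts at each stage are already being reported, so the problem can be repaired without redesign.

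**Conclusion.** The point holds as a mismatch between the stated analysis set and the primary endpoint, made worse by sections that use conflicting populations. Followed as written, the plan yields prevalence among symptomatic consenters and not in chronic liver disease.

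The choice of denominator moves the result 2.5-fold at the planned rates and 8.3-fold at the early pilot uptake. The direction of the bias is not identified. On pilot counts the literal set is 1.96 times too high with no PoPH in questionnaire-negatives, correct at about 49% asymptomatic cases, and 0.78 of the true value at 60%.

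These error sizes assume that patients with UCG represent all questionnaire-positive patients and that asymptomatic in the cited source means questionnaire-negative here. Neither can be checked from the article. Because the primary endpoint is affected and the repair is cheap, it should be made before the analysis.

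**What to change.** 1. Take symptom positivity out of the analysis-set definition and state it as the trigger for UCG. Correct the Discussion's description of the 300 respondents, and say whether the 2,500 are respondents or enrolled patients.
2. Define the primary denominator as every patient with chronic liver disease given the questionnaire. Log the counts at each stage: questionnaire given, positive, consented, UCG done, referred, catheterized, PoPH.
3. Estimate prevalence as P(questionnaire positive) × P(PoPH | positive, UCG done), with a 95% CI that carries both stages. Adjust simply for UCG uptake only if case numbers allow.
4. Label the result as prevalence of symptom-detected PoPH. It is a lower bound for chronic liver disease under the assumption that those who had UCG represent all questionnaire-positive patients.
5. Add a sensitivity range that divides the estimate by (1 - *a*) for asymptomatic shares *a* of, for example, 0 to 60%.
6. Report the proportion among symptomatic patients separately, under that name.

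**Cost.** Protocol wording; a screening log, with ethics approval to keep data on respondents who were negative or declined, since consent is now sought only after a positive answer; and a somewhat wider interval, because only patients who had UCG inform the second stage.

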#### Exclusion criteria

Patients exhibiting any of the following criteria are excluded: 1) having a history of chronic heart failure, 2) having PAH due to any other cause, and 3) unable to be followed at our hospital, as presented in Table 1.

#### Etiology of chronic liver diseases

The etiologies of the chronic liver diseases included in this study are as follows: 1) hepatitis B virus (HBV) infection defined as HBe antigen-positive asymptomatic carriers, chronic hepatitis, HBe antigen-negative inactive carriers, and HBs antigen-negative clinical remission regardless of cirrhosis status, according to the guidelines provided by the Japan Society of Hepatology [14], 2) HCV infection including patients with persistent HCV infection and with post-HCV eradication in a sustained virological response, based on the guidelines provided by the Japan Society of Hepatology [15], 3) ALD including patients with a drinking habit (ethanol >60 g/day for men, ethanol >40 g/day for women) and persistent elevation of aminotransferase and γ-GTP, according to the guidelines established by the Japanese Society of Gastroenterology [16], 4) nonalcoholic fatty liver disease (NAFLD)/nonalcoholic steatohepatitis (NASH), according to the guidelines provided by the Japanese Society of Gastroenterology and the Japan Society of Hepatology [17], and 5) autoimmune liver disease including AIH, primary biliary cholangitis (PBC), and primary sclerosing cholangitis (PSC), based on the guidelines provided by the Japan Society of Hepatology [18–20].

### Trial design and follow-up

Participant registration for the study will run from October 1, 2020 to October 30, 2022. All participants will answer the written questionnaire described in Table 2 in the outpatient clinic of Shinshu University Hospital. If at least one question is positive, informed consent will be obtained from the individual for enrollment in the study. Then, the participant will undergo ultrasound echocardiography (UCG) as a first-line screening. If the participant exhibits UCG-positive findings indicating a high probability of PoPH as shown in Tables 3 and 4, the patient will be referred to a cardiologist in the Department of Cardiology for further evaluation, whereby a definitive diagnosis will be made by right heart catherization findings as shown in Table 5. The frequency of PoPH patients will be analyzed (Observational study 1) along with the etiology of PoPH in chronic liver disease (Observational study 2).

**Table 2 pone.0249435.t002:** Standardized questionnaire on symptoms suggesting portopulmonary hypertension (translated from Japanese; respondents indicate “yes” or “no”).

1) Do you feel you cannot work comparably to other people of the same age and gender?
2) Do you feel you cannot move as fast as other people do?
3) Do you feel you cannot move at the same pace as others?
4) Do you need rest when climbing stairs or carrying heavy loads?
5) Do you ever experience shortness of breath?
6) Do you ever experience faintness?
7) Do you ever experience tiredness and/or persistent malaise?
8) Do you ever experience dizziness and/or vertigo?
9) Do you ever experience facial edema and/or pretibial edema?

**Table 3 pone.0249435.t003:** Echocardiographic probability of PAH in patients having symptoms indicative of PAH [21].

Peak tricuspid regurgitation velocity (m/s)	Presence of other echo PH signs	Echocardiographic probability of PAH
≤2.8	No	Low
≤2.8	Yes	Intermediate
2.9–3.4	No	
2.9–3.4	Yes	High
>3.4	Not required	

Abbreviations: PAH, pulmonary artery hypertension; PH, pulmonary hypertension.

**Table 4 pone.0249435.t004:** Echocardiographic signs suggesting PAH used to assess the probability of PAH in addition to tricuspid regurgitation velocity measurement in Table 3 [21].

A: Ventricles	B: Pulmonary artery	C: Inferior vena cava and right atrium
Right ventricle:left ventricle basal diameter ratio >1.0	Right ventricular outflow doppler acceleration time <105 msec and/or midsystolic notching	Inferior cava diameter >21 mm with decreased inspiratory collapse (<50% with a sniff or <20% with quiet inspiration)
Flattening of the interventricular septum (left ventricular eccentricity index >1.1 in systole and/or diastole)	Early diastolic pulmonary regurgitation velocity >2.2 m/sec	Right atrium area (end-systole) >18 cm^2^
	Pulmonary artery diameter >25 mm	

Abbreviations: PAH, pulmonary artery hypertension.

**Table 5 pone.0249435.t005:** Diagnosis criteria of PoPH [21–23].

1. Existence of PAH by right heart catheraization
a. Mean pulmonary artery pressure (mPAP) ≥ 25mmHg
b. Pulmonary artery wedge pressure (PAWP) ≤ 15mmHg
2. Existence of portal hypertension
Hepatic vein pressure gradient (HVPG) ≥ 5mmHg
3. Rule out of other etiology of PAH

Abbreviations: PoPH, portopulmonary hypertension; PAH, pulmonary artery hypertension.

When a PoPH diagnosis is made, the following clinical data will be collected: etiology of liver disease, age, gender, height, body weight, history of medication, drinking habit, smoking habit, New York Heart Association (NYHA) classification, 6-minute walking distance, FibroScan^®^ results, blood and urine data, thoracic-abdominal enhanced computed tomography findings, right heart catheter findings (mean pulmonary artery pressure, right atrial pressure, pulmonary artery wedge pressure, cardiac index, cardiac output, pulmonary vascular resistance, and mixed venous oxygen saturation), and echocardiographic findings.

Upon diagnosis, PoPH treatment will be initiated by a cardiologist based on the guidelines for pulmonary hypertension issued by the Japanese Circulation Society [22]. Patients will be evaluated every six months for blood and urine findings, abdominal ultrasonography results, and clinical symptoms. UCG will be performed on a yearly basis. The observation period will be five years from the time of patient enrollment and will end if the patient dies or becomes lost to follow-up. Ultimately, the 5-year survival rate of PoPH patients and factors associated with survival will be analyzed (Observational study 3).

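### The PAH part of the case definition sets no resistance or flow criterion, so low-resistance, high-flow patients can enter the primary endpoint; prespecify a PVR-based analysis classification from data already collected

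*Protocol article*

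**What the plan says.** Under Trial design and follow-up, patients with a high echocardiographic probability go to a cardiologist, and "a definitive diagnosis will be made by right heart catherization findings as shown in Table 5". Table 5 has three items:

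1. PAH at catheterization: "a. Mean pulmonary artery pressure (mPAP) ≥ 25mmHg" and "b. Pulmonary artery wedge pressure (PAWP) ≤ 15mmHg".
2. Portal hypertension: "Hepatic vein pressure gradient (HVPG) ≥ 5mmHg".
3. Other causes of PAH ruled out, with no rule stated for how.

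The Endpoints section builds on this: "The primary endpoint in this study is the prevalence of PoPH in Japanese patients with chronic liver disease and its etiology". The secondary endpoint, five-year survival, is measured in the same cases.

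Once a case is diagnosed, the catheter data recorded include "cardiac index, cardiac output, pulmonary vascular resistance, and mixed venous oxygen saturation". The Statistical analysis section carries forward a shorter list: "right heart catheter findings (mean pulmonary artery pressure, right atrial pressure, pulmonary artery wedge pressure, and cardiac index".

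**The concern.** Pressure in the pulmonary artery can rise because resistance is high or because flow is high. Item 1 of Table 5 looks at pressure alone, so it cannot tell the two apart. The Introduction names a hyperdynamic pulmonary circulation among the factors linked to PoPH, so the authors regard flow as relevant in this population.

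If flow-driven cases are accepted, the prevalence numerator can include patients without raised vascular resistance. The etiology distribution and the Kaplan–Meier and Cox analyses would then describe a mixture. The protocol expects very low prevalence, so a few such patients could matter. A resistance limit chosen after the cases are known would be open to the charge of having been picked to suit the result.

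**Working it through.** **Inputs from the protocol article.** mPAP at least 25 mmHg, PAWP at most 15 mmHg and HVPG at least 5 mmHg (Table 5); PVR and cardiac output recorded for diagnosed cases (Trial design and follow-up). The plan gives no PVR figure to reproduce.

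**Assumed input.** Cardiac output (CO) of 4 to 10 L/min. The document gives no output values; these only show how the identity behaves.

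**Step 1. What item 1 implies for resistance.** PVR (Wood units) = (mPAP − PAWP)/CO. All rows below satisfy item 1.

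| mPAP / PAWP (mmHg) | Gradient | CO 4 | CO 5 | CO 8 | CO 10 |
|---|---|---|---|---|---|
| 25 / 15 | 10 | 2.5 | 2.0 | 1.25 | 1.0 |
| 25 / 10 | 15 | 3.75 | 3.0 | 1.88 | 1.5 |
| 30 / 15 | 15 | 3.75 | 3.0 | 1.88 | 1.5 |
| 35 / 15 | 20 | 5.0 | 4.0 | 2.5 | 2.0 |

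For example, (25 − 15)/8 = 1.25 and (35 − 15)/10 = 2.0. For any fixed pair of pressures, PVR differs by a factor of 10/4 = 2.5 across these outputs. Item 1 therefore sets no lower limit on resistance, and a rise in flow alone can meet it.

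**Step 2. Whether another step closes the gap.**

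- HVPG measures the portal side. It says nothing about pulmonary flow against resistance.
- Item 3 excludes other causes of PAH but states no flow or resistance rule. A cardiologist may remove some patients by judgement, but an unstated judgement does not give a reproducible numerator.
- The echocardiographic screen (Tables 3 and 4) starts from tricuspid regurgitation velocity, which reflects pressure. Above 3.4 m/s it needs no further sign; between 2.9 and 3.4 m/s it needs others. It may thin out such patients but sets no resistance criterion.

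**Step 3. Whether the recorded data suffice.** PVR and cardiac output are listed for patients already diagnosed. An added criterion can only remove Table 5 cases and never add one, so data on diagnosed cases are enough to reclassify them.

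**Step 4. How the endpoint would move.** If a share f of Table 5 cases has low resistance, a restricted prevalence is p × (1 − f). Both inputs here are assumptions: the 1–2% that the Introduction cites for cirrhosis is applied to the target of 2,500, and f is varied from 10% to 50%.

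- p = 1% gives 25 cases. Restricted: 22.5 (0.9%) at f = 10%, 12.5 (0.5%) at f = 50%.
- p = 2% gives 50 cases. Restricted: 45 (1.8%) at f = 10%, 25 (1.0%) at f = 50%.

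This shows sensitivity only. Nothing in the document fixes f.

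**The case against.** The strongest reply is that the document nowhere says raised resistance is part of PoPH. Table 5 cites sources [21–23], which are not available here, so whether it departs from them cannot be checked. This stands: no cut-off can be supplied from outside, and calling a low-resistance case a false positive presupposes a resistance-based definition. What remains is that the definition does not separate the two mechanisms and the plan does not say why.

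Several further points on the other side also stand.

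- A reader might infer that prevalence will be biased upward overall. The document does not support that. Enrolment requires symptoms, while the Discussion reports that up to 60% of PoPH patients had none, and only high-probability echocardiograms are referred. Both can lower the count, so the net direction is not shown.
- A reader might infer that the error gathers in advanced cirrhosis. The document gives no cardiac output by disease stage.
- The Introduction presents hyperdynamic circulation as possible pathogenesis, not as a mimic to be excluded. It shows relevance and no more.
- Leaving PVR off the analysis list is a small matter, since mPAP, PAWP, cardiac index, height and weight are all listed and PVR is essentially derivable.
- Treatment starts upon diagnosis, so altering Table 5 itself would change who is treated. That is a clinical matter outside this point.

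The information also stays recoverable after the fact, and an analysis plan not shown could stratify by PVR. That lowers the severity. It does not remove the point, because the article states the case definition in full, with thresholds.

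**Conclusion.** The point holds in a limited form. The PAH item of the case definition rests on two pressures, and the other Table 5 items do not distinguish flow from resistance. Low-resistance, high-flow patients can therefore count as cases: exactly on the two limits, PVR is 2.0 Wood units or less at any output of 5 L/min or more.

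That they can count follows from the identity and Table 5. The example outputs are assumptions. How many will count is unknown, so no percentage distortion of prevalence, etiology or survival can be claimed. It would also go too far to say that the definition uses only mPAP and wedge pressure, since portal hypertension and exclusion of other causes are required too. Severity: should be fixed, because the remedy is cheap and protects the interpretation of the primary endpoint.

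**What to change.** Leave the clinical diagnosis and treatment pathway as they are. In the Statistical analysis section:

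1. Prespecify, for endpoint analysis only, a classification of Table 5 cases by PVR. Take the limit from the sponsor's own cited sources [21–23], or state why no limit is used. This review proposes no cut-off.
2. Report prevalence, etiology and survival twice: for all Table 5 cases, and without those that meet only the mPAP and PAWP limits. Label the second group plainly.
3. Fix the classification before the case data are examined.

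The cost is a few lines of text. PVR and cardiac output are already recorded for each diagnosed case, so no new measurement is needed. The only downside is a possibly smaller case count, and so less precision, in the restricted analysis.
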